## Abstract

**Introduction:**

In high mortality settings, prophylactic azithromycin has been shown to improve birth weight and gestational age at birth when administered antenatally, to reduce the incidence of neonatal infections when administered intrapartum, and to improve survival when administered in infancy. Questions remain regarding whether azithromycin can prevent stillbirths, and regarding the optimal strategy for the delivery of azithromycin to pregnant women and their infants.

**Methods and analysis:**

Sauver avec l’Azithromycine en Traitant les Femmes Enceintes et les Enfants (SANTE) is a 2×2 factorial, individually randomised, placebo-controlled, double-masked trial in rural Mali. The primary aims are: (1A) to assess the efficacy of antenatal and intrapartum azithromycin on a composite outcome of stillbirths and infant mortality through 6–12 months and (1B) to assess the efficacy of azithromycin administered concurrently with the first and third doses of pentavalent vaccines (Penta-1/3) on infant mortality through 6–12 months. Pregnant participants (n=49 600) and their infants are randomised 1:1:1:1 to one of four treatment arms: (1) mother and infant receive azithromycin, (2) mother and infant receive placebo, (3) mother receives azithromycin and infant receives placebo or (4) mother receives placebo and infant receives azithromycin. Pregnant participants receive three single 2 g doses: two antepartum and one intrapartum. Infants receive a single 20 mg/kg dose at the Penta-1 and 3 visits. An additional cohort of 12 000 infants is recruited at the Penta-1 visit and randomised 1:1 to receive azithromycin or placebo at the same time points. The SANTE trial will inform guidelines and policies regarding the administration of antenatal and infant azithromycin using routine healthcare delivery platforms.

**Ethics and dissemination:**

This trial was approved by the Institutional Review Board at the University of Maryland School of Medicine (Protocol #HP-00084242) and the Faculté de Médecine et d’Odonto-Stomatologie in Mali. The findings of this trial will be published in open access peer-reviewed journals.

**Trial registration number:**

NCT03909737.

STRENGTHS AND LIMITATIONS OF THIS STUDYThe trial is conducted in a low-resource setting with high rates of stillbirth and infant mortality.The intervention is delivered through the public healthcare system, relying on the existing infrastructure for routine primary care.The trial assesses multiple time points for the administration of azithromycin to prevent infant mortality (antenatal, intrapartum and infant).The trial includes ancillary studies to assess antimicrobial resistance and to investigate potential mechanisms of action of azithromycin in subsets of participants.The trial is unable to reliably determine individual causes of stillbirth and infant death.

## Introduction

Despite significant improvements in child survival over the past two decades, global rates of stillbirth and infant mortality remain unacceptably high. Of the 5.2 million under-5 deaths in 2019, 3.9 million (75%) occurred within the first 12 months of life and 2.4 million (45%) within the first month.^1^ More than half of global under-5 deaths and 42% of the estimated 2 million global stillbirths occur in sub-Saharan Africa, where approximately 60% of child mortality is estimated to be due to preventable infectious causes.^2 3^ Within the Child Health and Mortality Prevention Surveillance (CHAMPS) network, postmortem sampling identified at least one infectious condition in the causal chain leading to death in 53% of neonatal deaths and 17% of stillbirths.^4^ However, the causes of most stillbirths in low-income and middle-income countries are unexplained, owing to insufficient data and the failure to adopt a standardised classification system for perinatal cause of death.^5–7^ While malaria and syphilis are the most commonly recognised infectious causes of stillbirth, postmortem sampling in CHAMPS identified *Escherichia coli*/*Shigella*, *Streptococcus agalactia* and *Enterococcus faecalis* as other potentially significant infectious causes.^4 8^

An effective new strategy to prevent stillbirths and infant deaths that could be incorporated into routine primary healthcare services would be a major achievement in global health. One promising intervention to improve child survival is the prophylactic administration of the antibiotic azithromycin, a second-generation broad-spectrum macrolide that is used in mass drug administration (MDA) campaigns to control trachoma.^9^ Current WHO guidelines recommend consideration of biannual MDA-azithromycin for infants aged 1–11 months to improve survival in high mortality settings.^10^ These guidelines are based on data from three randomised controlled trials (RCTs), two of which found a statistically significant reduction in all-cause mortality among children randomised to receive azithromycin.^11–13^ There are insufficient data to support global policy recommendations for prophylactic azithromycin in pregnancy, although it has also been shown to reduce the incidence of preterm birth and low birth weight when administered antenatally, and to prevent neonatal infections when administered intrapartum.^14 15^ Further evidence is needed to understand (1) whether antenatal and intrapartum azithromycin can prevent stillbirths and early infant deaths, (2) the optimal method and timing of azithromycin administration in infancy to prevent mortality and (3) whether the survival benefit observed in two randomised MDA-azithromycin trials can be replicated in other settings.

Here, we describe the protocol for an individually randomised, placebo-controlled,2×2 factorial trial to determine (1) the effect of antenatal and intrapartum azithromycin on stillbirths and infant mortality and (2) the effect of azithromycin on infant mortality when delivered with the first and third doses of diphtheria, tetanus, pertussis, hepatitis and Hib-containing (ie, pentavalent) vaccine. The trial will take place in Mali, a low-income West African country with high stillbirth, neonatal and infant mortality.

## Methods and analysis

### Study design, objectives and hypotheses

Sauver avec l’Azithromycine en Traitant les Femmes Enceintes et les Enfants (SANTE) is an individually randomised, placebo-controlled, double-masked trial. Using a 2×2 factorial design with four treatment arms, SANTE will simultaneously assess coprimary aim 1A: whether azithromycin administered at routine antenatal care (ANC) visits (second and/or third trimester) and at delivery reduces a composite outcome of stillbirth and infant mortality, and coprimary aim 1B: whether azithromycin administered to infants concurrently with the first and third doses of pentavalent vaccine (Penta-1 and Penta-3) reduces mortality from the time of the first dose through 6–12 months of life. We will enrol 49 600 pregnant participants who will be randomised to receive 2 g azithromycin or placebo as a single oral dose twice during pregnancy and at delivery, for up to three total doses. Their infants will be randomised to receive 20 mg/kg azithromycin or placebo as a single oral dose at their routine Penta-1 and Penta-3 vaccination visits (figure 1). According to the national routine immunisation schedule, these vaccination visits occur at approximately 6 and 14 weeks of age, respectively. Infants are followed through at least 6 months and up to 12 months of age. To increase statistical power for aim 1B, a separate cohort of 12 000 infants, the infant-only cohort, is recruited at the Penta-1 visit. Infants enrolled in the infant-only cohort are randomised, dosed and followed in the same manner as those born to pregnant participants. Participant enrolment commenced in September 2020 and is expected to be complete by April 2023.

**Figure 1 F1:**
[figure not shown]
SANTE study design. Flow diagram to illustrate randomisation and treatment groups for the 2x2 factorial mother–infant cohort and the infant-only cohort. ‘Penta 1’ and ‘Penta 3’ correspond to the first and third doses of pentavalent vaccine (ie, diphtheria, tetanus, pertussis, hepatitis and Hib-containing vaccine). SANTE, Sauver avec l’Azithromycine en Traitant les Femmes Enceintes et les Enfants.

We hypothesise that the composite outcome of stillbirths and infant deaths will be lower in infants whose mothers were randomised to receive azithromycin in pregnancy compared with those randomised to receive placebo, and that mortality will be lower in infants who were randomised to receive azithromycin at first and third pentavalent vaccination visits compared with those randomised to receive placebo.

The trial has been registered at ClinicalTrials.gov (NCT03909737). The WHO trial registration data set can be found in online supplemental appendix table 1. Study recruitment began in September 2020 and is anticipated to end by April 2023. All follow-up will be completed within 12 months of enrolling the last pregnant participant.

10.1136/bmjopen-2022-067581.supp1Supplementary data

### Study setting

SANTE is conducted by investigators at the Centre pour le Développement des Vaccins, Mali (CVD-Mali), an ongoing collaboration between the University of Maryland School of Medicine and the Malian Ministry of Health. For the past decade, much of northern and central Mali has been besieged by political instability and violence. The southwestern region of Sikasso, recently divided into the independent regions of Sikasso and Koutiala, had a reported infant mortality rate of 67 per 1000 live births in 2018.^16^ It was selected as the study setting due to its high under-5 mortality, moderate utilisation of ANC, moderate routine immunisation coverage, and relative security (online supplemental appendix table 2). Malaria is endemic in southwestern Mali, and standard of care for pregnant women is at least three doses of sulfadoxine-pyrimethamine (SP) intermittent preventive treatment (IPTp). Children aged 3–59 months receive a combination of monthly SP plus amodiaquine as seasonal malaria chemoprophylaxis (SMC) for 4 months during peak malaria transmission season (July–October). Each monthly SMC dose is composed of one directly observed dose and two additional doses to be administered at home by the caregiver. In Sikasso, IPTp coverage with three or more doses is 26.8%, and 54% of age-eligible children receive one or more doses of SMC each year.^16^ Within the Koutiala and Sikasso regions, the districts of Koutiala, Kignan and Niena were selected for study operations. These districts represent areas with a high burden of paediatric illness and have populations of sufficient size to meet the study’s enrolment requirement within the target time frame.

### Recruitment

Mali’s decentralised health system operates at national, regional, district (cercle), health area (aire de santé) and community levels. Each district is served by a referral centre (Centre de Santé de Référence, CSREF) and each aire de santé is served by one or more community health centres (Centres de Santé Communautaire, CSCOMs). SANTE study teams are embedded at all operational and accessible CSREFs and CSCOMs in the Koutiala, Kignan and Niena districts. Many rural CSCOMs conduct regular community outreach operations (stratégie avancée), sending mobile units to remote health outposts to provide ANC and immunisation services. Study participants are recruited at antenatal or immunisation visits at participating CSREFs and CSCOMs, or from remote health posts as part of the stratégie avancée.

### Inclusion and exclusion criteria

Pregnant individuals seeking ANC are eligible to be enrolled if they have reached at least 14 weeks gestation and are not in active labour. If ultrasound dating is unavailable, participants are deemed eligible if the fundus can be palpated at two or more finger breadths above the pubic symphysis, a proxy measurement for a gestational age of at least 14 weeks.^17^ Infants in the infant-only cohort are eligible to be enrolled if they are at least 6 weeks and fewer than 12 months of age and are presenting to a study facility to receive Penta-1 vaccine. Additional enrolment criteria are provided in table 1.

**Table 1 T1:** Inclusion and exclusion criteria

Enrolment criteria: Pregnant women and unborn infants enrolled in mother–infant cohort	
Inclusion criteria	Exclusion criteria
Participant is estimated to be ≥14 weeks gestation according to the study algorithm and is presenting at a study facility	Participant is in active labour, as defined by study standard operating procedures
Participant understands and can comply with planned study procedures, as determined by the study staff	Participant has a known allergy to macrolide antibiotics
Participant or legal authority has provided informed consent prior to initiation of any study procedures	Participant has a condition that, in the opinion of the investigator, might compromise his or her well-being, or affect the ability of the participant to comply with study procedures
Participant intends to reside in the study area until her newborn infant is at least 6 months old	Participant is currently being treated with a macrolide antibiotic for a medical condition (this can be a temporary exclusion if the drug is later discontinued)

Enrolment criteria: Infants enrolled in the infant-only cohort	
Inclusion criteria	Exclusion criteria
Participant is presenting for Penta-1 vaccination at a study facility	Participant has a known allergy to macrolide antibiotics
Participant is at least 6 weeks of age, and fewer than 12 months of age	Participant has a condition that, in the opinion of the investigator, might compromise his or her well-being, or affect the ability of the participant to comply with study procedures
Participant’s parent/guardian understands and can comply with the study procedures, as determined by the study staff	Participant is currently being treated with a macrolide antibiotic for a medical condition (this can be a temporary exclusion if the drug is later discontinued)
Participant’s parent/guardian has provided informed consent prior to initiation of any study procedures	
Participant’s parent/guardian intends to reside in the study area until infant is at least 6 months old	

### Randomisation and masking

Treatment allocation is stratified by enrolment facility and randomised in permuted blocks of varying sizes (online supplemental appendix). In the mother-infant cohort, participants are randomised 1:1:1:1 to one of four possible treatment assignments(figure 1). Infants born to mothers enrolled in the mother–infant cohort are randomised when the mother is enrolled, that is, before the infant is born. Infants born to multiple gestation pregnancies are randomised to the same treatment group. In the infant-only cohort, infants are randomized 1:1 to receive azithromycin or placebo.

Participants are randomised at enrolment using barcoded labels that are preprinted with a sequential participant identification number and randomisation assignment. The randomisation assignment corresponds to a masked treatment bin, denoted by a letter of the alphabet, and preprinted on every study medication bottle. Participants, field workers and study investigators are unaware of the link between the bin letters and the treatment assignments.

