### Statistical considerations

#### Sample size and power

The original power calculations for the primary aims were based on anticipated stillbirth and infant mortality rates in the Sikasso/Koutiala regions estimated from published data at the time the trial was being designed (table 3). Analysable endpoints were expected for at least 85% of enrolled participants. After the trial was initiated, observed stillbirth and infant mortality rates in the study population, pooled across blinded treatment arms, were used to update the sample size targets from 33 600 to 49 600 in the mother–infant cohort and from 8500 to 12 000 in the infant-only cohort (online supplemental appendix table 4). The resulting sample sizes are large, as infant mortality even in Mali is relatively rare, resulting in somewhat small absolute differences. For example, for Aim1B, with a baseline IMR of 9/1000, a 24.7% relative reduction means detecting an absolute reduction of less than 3 deaths per 1000.

**Table 3 T3:** Sample size assumptions and minimum detectable relative reductions for the coprimary aims

	Original	Revised
Target sample size, mother–infant cohort	33 600*	49 600

Aim 1A. Effect of intervention on composite outcome of stillbirths and infant deaths from birth to 12 months		
Baseline combined stillbirth and infant mortality rate	105/1000†	74/1000†
Minimum detectable relative mortality reduction, comparing azithromycin to placebo treatment arms		
80% power	9.5%	8.7%
90% power	10.9%	10.1%

Aim 1B. Effect of intervention on infant deaths from first dose (approx. 6 weeks) to 12 months		
Infant mortality rate	28/1000‡	9/1000‡
Minimum detectable relative mortality reduction, comparing azithromycin to placebo treatment arms		
80% power	18.6%	24.7%
90% power	21.4%	28.3%
With addition of infants from the infant-only cohort§		
80% power	16.6%	22.3%
90% power	19.1%	25.6%

*In the original sample size calculation, 15% anticipated loss to follow-up (LTFU) meant that 28 560 infants were expected to have analysable endpoints.

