†Original assumed composite baseline stillbirth and infant mortality was 105 deaths per 1000 births, calculated from 33 stillbirths/1000 births^55^ and 74.8 infant deaths per 1000 live births (Sikasso data, Mali 2012 Demographic and Health Survey [DHS] report^56^), assuming that 6–11 months mortality data are available for 90% of infants and subtracting stillbirths from the live birth denominator. Revised observed composite stillbirth and infant mortality rate in the study population is 74 deaths per 1000 births.

‡Original baseline infant mortality rate after 6 weeks of age was 28 per 1000 live births (Sikasso data, 2012 Mali DHS report) assuming that 6–11 months mortality data are available for 90% of infants; revised infant mortality rate after 6 weeks of age was updated to 9 deaths per 1000 live births based on observed mortality in the study population.

§Original target sample size for infant-only cohort was 8500, assuming 7650 analysable (10% LTFU); revised target sample size 12 000.

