#### Analysis of primary aims

The primary analysis for aim 1A will be according to the intention-to-treat (ITT) principle. All live born infants and all stillborn infants born at ≥22 weeks gestation or weighing at least 500 g will be included, with infants classified according to the treatment assignment made at the time of the mother’s enrolment. For aim 1B, the primary analysis will be according to modified ITT, beginning from the first assigned dose. Sensitivity analyses of the two aims will be modified as-treated. If a mother or infant receives at least one study dose of azithromycin, they will be classified as being in the corresponding azithromycin-receiving study arm. Percent lost to follow-up will be compared across treatment arms for each intervention. Among those lost to follow up, baseline characteristics will be compared to assess whether loss is differential by intervention or by treatment arm. In the 2×2 factorial design, the primary analyses will fit a Cox proportional hazards regression model with two indicator variables for the two interventions, with censoring at the earliest of documented refusal for further participation, death, last study contact or recorded source of vital status, or attainment of 12 months of age. The study is not powered to detect a statistical interaction effect between the two interventions, but if it is important (p<0.05 or ratio of HRs >1. 5 or <0.67), results for all four study arms will also be reported. For primary aim 1A, the analysis timeline will be calculated from delivery, with stillbirths assigned day 0.1. For primary aim 1B, the timeline will start at the receipt of the first infant dose. For a measure of overall public health impact on infant mortality, a supplementary analysis will be done with the timeline starting at the live birth.

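### Facility is a randomisation stratum but is not in the primary Cox model as stated; stratifying by it is a small, free gain, mainly for aim 1A

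*Protocol article*

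**What the plan says.** Under Randomisation and masking: "Treatment allocation is stratified by enrolment facility and randomised in permuted blocks of varying sizes". In the mother–infant cohort "participants are randomised 1:1:1:1 to one of four possible treatment assignments"; in the infant-only cohort "infants are randomized 1:1 to receive azithromycin or placebo". Facility is therefore a stratification factor in both cohorts, and the two cohorts are randomised separately.

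Under Recruitment: "SANTE study teams are embedded at all operational and accessible CSREFs and CSCOMs in the Koutiala, Kignan and Niena districts". Enrolment also takes place at remote health posts during outreach.

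Under Analysis of primary aims: "the primary analyses will fit a Cox proportional hazards regression model with two indicator variables for the two interventions". That section also fixes the censoring rule, the time origin for each aim and the day assigned to stillbirths. It names no facility stratum, covariate or frailty term, and it does not say that facility is excluded.

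**The concern.** A design that balances arms within facility is normally analysed with facility in the model. If facilities differ in baseline risk and the model leaves them out, two small things follow. The model-based variance takes no account of the balance that the blocks achieved, so the test is a little conservative. The marginal hazard ratio also lies slightly closer to 1 than the within-facility hazard ratio. Both work against detecting an effect.

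This deserves a line because the effects sought are small (8.7% for aim 1A at 80% power) and participants are costly: the blinded pooled event rates "were used to update the sample size targets from 33 600 to 49 600 in the mother–infant cohort and from 8500 to 12 000" (the last pair being the separately recruited infants). Stratifying the model needs no further participants or data.

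**Working it through.** **Inputs from the article.** Aim 1A: 49 600 participants; "Revised observed composite stillbirth and infant mortality rate in the study population is 74 deaths per 1000 births"; detectable reduction 8.7%. Aim 1B: 49 600 + 12 000 = 61 600 infants; "revised infant mortality rate after 6 weeks of age was updated to 9 deaths per 1000 live births"; detectable reduction 22.3%. Allocation is 1:1 at each factorial margin.

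**Assumptions.** Two-sided alpha of 0.05 (the final alpha is not stated); 30, 60 or 120 facilities; SD of the facility log hazard of 0.3, 0.5 or 0.8; full follow-up of everyone enrolled. The article gives neither the number of facilities nor the variation between them.

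**Step 1: reproduce Table 3.** Two-proportion formula with pooled variance under the null and n per arm, at 80% power:

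p1 − p2 = [1.960·√(2·p̄(1−p̄)) + 0.842·√(p1(1−p1) + p2(1−p2))] / √n

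- Aim 1A: n = 24 800, p1 = 0.074, p2 = 0.0675. Difference = (1.960 × 0.3627 + 0.842 × 0.3626)/157.5 = 0.00645, and 0.00645/0.074 = 8.7%. Table 3 has 8.7%.
- Aim 1B with the infant-only cohort: n = 30 800, p1 = 0.009, p2 = 0.0070. Difference = (1.960 × 0.1259 + 0.842 × 0.1259)/175.5 = 0.00201, and 0.00201/0.009 = 22.3%. Table 3 has 22.3%.

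The other Table 3 entries also match to rounding. The stated power therefore takes no credit for stratification.

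**Step 2: what sets the reported standard error.** With rare events, SE(log HR) ≈ √(1/d1 + 1/d2), where d1 and d2 are the deaths per arm.

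- Aim 1A: d1 = 24 800 × 0.074 = 1835; d2 = 1835 × 0.913 = 1676; SE = 0.034.
- Aim 1B: d1 = 30 800 × 0.009 = 277; d2 = 277 × 0.777 = 215; SE = 0.091.

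Facility does not enter this expression, so adding it should not narrow the reported interval.

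**Step 3: simulation.** Each scenario had 20 000 replicates, with arms balanced within facility. An unstratified proportional-hazards estimate (rate ratio) was compared with a facility-stratified conditional-likelihood estimate. Log hazard ratios and standard errors below are for aim 1A with 60 facilities; the other columns span 30 to 120 facilities.

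| SD | Mean log HR, unstratified → stratified | Reported SE, both models | Power gain 1A (points) | Power gain 1B (points) | Type I error 1A, unstratified |
|---|---|---|---|---|---|
| 0.3 | −0.0910 → −0.0913 | 0.0339 | 0.23–0.26 | 0.03–0.05 | 0.047–0.053 |
| 0.5 | −0.0904 → −0.0912 | 0.0340 | 0.53–0.66 | 0.08–0.10 | 0.047–0.050 |
| 0.8 | −0.0885 → −0.0907 | 0.0345 | 1.47–1.69 | 0.10–0.23 | 0.0435–0.0445 |

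The reported SE is the same in both models. What stratifying changes is the estimate: at SD 0.8 the attenuation is 1 − 0.0885/0.0907 = 2.4%. Also at SD 0.8, the stratified test has type I error of 0.049 to 0.050.

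The 8.7% was applied to the hazard, so unstratified power for aim 1A was 73% to 77% rather than 80% (an event-based formula needs about 9.0% for 80% power). Both models face the same data, so this does not affect the comparison. The aim 1B runs did not include cohort as a separate factor.

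**Step 4: analytic check on the conservatism.** The between-facility share of the outcome variance is p(exp(SD²) − 1)/(1 − p). At p = 0.074 and SD 0.8 it is 0.0799 × 0.896 = 7.2%. The effective critical value is 1.96/√(1 − 0.072) = 2.03, a two-sided alpha of about 0.042, close to the simulated 0.044.

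**Step 5: size in participants.** Starting from 80% power, the extra information is [(1.960 + z_new)/(1.960 + 0.842)]² − 1. Gains of 0.25, 0.6 and 1.6 points correspond to about 0.6%, 1.6% and 4.2%, or roughly 300, 770 and 2100 of the 49 600.

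**The case against.** The strongest reply is that this is a condensed article. The phrase about two indicators may only explain how the factorial design is coded (main effects without an interaction), and strata or covariates are commonly left to an analysis plan that is not shown here. That stands to this extent: one may say that the stated model does not include facility, but not that the trial will leave it out. The point survives as an improvement to a model that the article otherwise describes concretely.

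Four stronger readings are tempting, and the documents support none of them:

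- **The primary test is invalid.** It is not. Its type I error is at or slightly below nominal.
- **Stratifying would narrow the confidence interval.** The variance share in Step 4 is 0.75% to 5.1% for SD 0.3 to 0.7, which suggests a standard error 0.4% to 2.5% too wide. That measures how far the reported SE exceeds the true sampling variation of the unstratified estimate. It is not a saving in the reported SE, which stays the same.
- **The power in Table 3 is overstated for this reason.** Table 3 reproduces without any credit for stratification.
- **Facilities are known to differ strongly.** The article describes tiers of facility and outreach posts but gives no facility-level rates. The variation is an assumption.

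**Conclusion.** The mismatch holds, and its consequence is minor. As stated, the primary model does not reflect the factor on which allocation was stratified. If facilities differ in baseline risk, the result is a valid, slightly conservative test and a slightly attenuated hazard ratio.

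For aim 1A, stratifying gains 0.2 to 0.7 points of power at an SD of 0.3 to 0.5, and at most about 1.7 at 0.8, which is an extreme value. For aim 1B the gain is at most about 0.2 points, so there the case rests on following the design rather than on power. The direction is secure, because the gain was positive in every scenario with facility variation. The size depends on the assumed SD, number of facilities, full follow-up and two-sided alpha of 0.05.

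**What to change.** Before unblinding, specify that the primary Cox model keeps the two intervention indicators and stratifies the baseline hazard by enrolment facility for aim 1A, and by cohort and facility for aim 1B. Merge small facilities into their district by a threshold on enrolment numbers, written down in advance. A rule based on observed deaths should be avoided: it would define strata by the outcome and leave the model open until deaths are counted. Report the unstratified model as a sensitivity analysis. If the full analysis plan already stratifies by facility, aligning the published model statement with it is enough.

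The cost is a change of wording and a merging rule, with no new data or participants. The downside is a slight loss of information from strata with few or no events, mainly in aim 1B.
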